**Scans**

Scans will be obtained after 30 minute rest following the exercise. We will conduct neuroimaging sessions at times that are convenient for the participants. The combination of weekday and weekend scan options is chosen to optimize participation of participants who may work or be otherwise occupied during weekdays.

**Stimuli**

Cannabis stimulus

Content: We will use cannabis stimulus as described by Field et al.(Field, Eastwood et al. 2006). It includes pictures of cannabis in different forms and its use (people smoking joints) and related paraphernalia (e.g. bongs, pipes).

Food stimulus.

Content:Existing studies have shown clear brain effects of food cues that activate limbic, cognitive and reward regions. (Holsen et al., 2005). Killgore et al. (2003) have shown that caloric content of the food stimulus employed (i.e. high calorie versus low calorie) produces differential effects on regional brain activation. In this study we will use a stimulus set that includes only high caloric (high energy) food cues versus nature comparisons.

Paradigm:A block trial design is planned based upon our desire to employ a previously successful paradigm (Killgore et al., 2003) and because our goal is to maximize our chances of detecting activation differences (Birn et al., 2002). We will provisionally model our design on that of Killgore et al., 2003 by employing individual scanner runs of food images, cannabis-related images, and nature scenes. To control for non-specific aspects of visual stimulation, we will used blurred Gaussian images (similar to Holsen et al., 2005) as the fixation task. After Killgore et al., (2003) we will present images in 30-second blocks of 10 images each, displayed for 2500 milliseconds with a 500 millisecond interstimulus delay. To minimize the risk of participant motion effects precluding trial analysis, we will keep limit each scanner run to 3 minutes 30 seconds (i.e. 3 target stimulus 30 second blocks, 4 blurred Gaussian background blocks) minutes. The particular food, cannabis, or nature image sequences used will be randomized across scans and the order will be counterbalanced. Participants will have 3 scanner runs of the 3 minute 30 second stimulus display per exercise condition, so that each stimulus set will be seen 3 times/exercise condition. A different set of images will be used for the moderate and vigorous interventions and will be balanced across participants to neutralize order effects.

The total time in the scanner is about 1 hour/day.

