**Specific Aims**

1. To explore methodological factors involved in finding the relationship between PA and cannabis use.
   1. to examine the effects of cannabis and food cues on brain activation and craving in cannabis users and nonusers
   2. to examine the effects of vigorous exercise on brain activation and craving in response to cannabis and food cues.

Our working hypothesis is that the regional brain activation in response to drug cues will be different in cannabis users than in controls and that exercise will significantly alter brain responses to these cues in both groups. Our secondary hypothesis is that exercise will tend to normalize the abnormal brain activation observed in cannabis users.

Our expectation is that exercise will alter cue-responding in terms of brain activation or craving. It is possible that exercise may be a useful treatment in cannabis dependence. Future studies may examine this specific relationship.

There are no reports available exploring the relationship between physical activity and cannabis use.

Current data suggest that there are convergent findings regardingthe chronic and acute effects of cannabis on brain activity

1. **Inclusion/Exclusion Criteria**

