**Script for telephone screening is attached as Appendix B.**

**Informed consent form for patients and controls is included in IRB application.**

1. **Study Procedures**

We plan to enroll 35 participants. The study components will consist of an initial phone screen with the participant to verify provisional inclusion criteria. For applicants meeting provisional inclusion criteria, a screening visit will be scheduled for Informed Consent, explanation of study procedures, screening with study instruments and interviews, and an opportunity for a practice session in the mock MRI scanner. For applicants meeting inclusion criteria following screening, a study visit will be scheduled, preferably within 2 weeks of the screening day.

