Graphical and descriptive statistical techniques will be used to explore patterns of changes in activation within subjects to cannabis cues after the two exercise conditions (Primary Specific Aim 2). Tests of the changes in activation within key ROIs will be conducted using general linear modeling (GLM) methods that incorporate Generalized Estimation Equations (GEE) for parameter estimation of correlated data. The combination of GLM and GEE provides the most flexibility for modeling data of uncertain distribution, as well as for incorporating the mixed effects of between (cannabis vs. control) and within (prior exercise state). Again, effect sizes generated from these analyses will be used for statistical powering of planned subsequent RO1 research.

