**Power Estimates**

Because this is a pilot study to demonstrate feasibility, we estimate 10 subjects per group as reasonable sample size as this group size is commonly well in fMRI pilot studies. A key outcome of this study will be the calculation of effect sizes that will inform the powering of subsequent, larger studies. Commercially available statistical software packages (NCSS and PASS, number Cruncher Statistical Systems, Kaysville, Utah; SPSS, Chicago, IL; Stata, College Station, TX) will be used for data analysis.

1. **Privacy/Confidentiality Issues**

The participant research file will contain information concerning mental and physical health and experimentally derived data. All data collected in this study will be used specifically for research purposes. Should information that might have a bearing on the well being of participants be discovered, this information will be communicated to participants and, at the participant’s request, with their physician.

Electronic databases containing identifiable participant information will be password encoded. Written information containing participant identifiers (informed consent, lab results, participant payment, etc) will be stored in file cabinets in offices with the departments of Radiology and Psychiatry. Participants will be assigned an alphanumeric code that will be used to label all research data.

1. **Follow-up and Record Retention**

This pilot study is expected to last one year with data analysis continuing indefinitely. Records may be destroyed after data analysis is complete and all manuscripts are published, but records may be maintained indefinitely for future analysis. Emerging methods of analysis in fMRI research may permit the reanalysis of previously acquired data to extract new meaning.

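### Image set changes with exercise condition within each person, but balance within users and within controls is not stated and the Aim 2 model names no image-set term

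*Protocol*

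**What the plan says.** The Stimuli section (Study Procedures) assigns separate picture sets to the two exercise conditions: "A different set of images will be used for the moderate and vigorous interventions and will be balanced across participants to neutralize order effects". The sentence shortly before it deals with the order of presentation: "The particular food, cannabis, or nature image sequences used will be randomized across scans and the order will be counterbalanced". Neither sentence says whether the pairing of set with exercise condition is balanced separately among cannabis users and among controls.

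For Aim 2, General statistical methods says: "Tests of the changes in activation within key ROIs will be conducted using general linear modeling (GLM) methods", with GEE estimation. It gives as a reason the flexibility "as well as for incorporating the mixed effects of between (cannabis vs. control) and within (prior exercise state"). Image set is not mentioned. The same paragraph says that the resulting effect sizes will be used to power the next study.

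The comparison of exercise response between groups matters because of the Specific Aims: "Our secondary hypothesis is that exercise will tend to normalize the abnormal brain activation observed in cannabis users". On size, Power Estimates says "we estimate 10 subjects per group as reasonable sample size", while Study Procedures says "We plan to enroll 35 participants".

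**The concern.** A person who sees set A after vigorous exercise and set B after the other condition contributes a difference made of the exercise effect plus the A-minus-B picture difference. A person with the opposite pairing contributes the exercise effect minus that difference. One person's data cannot separate the two.

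Balancing the pairing over people cancels the picture difference in the pooled mean. It does not remove it from the spread of the within-person differences unless the model contains set. It cancels in the user-versus-control comparison only if the two groups have the same mix of pairings.

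Two things are at stake: the standardised effect sizes that this pilot is meant to hand on, and the comparison that carries the normalisation hypothesis, with 10 people per group. The protocol itself gives a reason to expect picture content to matter. The Stimuli section reports that the caloric content of food images changes regional activation, and it describes no step to equate the two sets.

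**Working it through.** **Plan's own figure.** The 10 per group rests on convention for fMRI pilots. No effect size, SD, alpha or power is given, so there is nothing to reproduce.

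**Inputs.** From the protocol: 10 users and 10 controls, different sets by condition, and a model naming group and prior exercise state. Assumed, because the documents give no figures: one scan per exercise condition per person; within-person error SD of 1; set difference d = 0.25, 0.5 or 1.0 of that SD; for power, an exercise effect of 0.7 SD or a group-by-exercise difference of 1.3 SD.

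**Model.** D = exercise effect (+ group-by-exercise term in users) + s·d + error, where D is the vigorous-minus-light difference and s = +1 or −1 according to which set went with vigorous exercise.

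**Step 1: pairing balanced 5/5 in each group, set not modelled.** The s·d terms sum to zero, so the raw estimates are unbiased. The residual sum of squares gains 20d², spread over 18 degrees of freedom. The estimated SE is therefore multiplied by about √(1 + 20d²/18), which is 1.03, 1.13 and 1.45. Simulation gives the average inflation relative to the model with set as 3, 13 and 46%.

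The population variance of D rises by the factor 1 + d². A standardised effect is then multiplied by 1/√(1 + d²) = 0.970, 0.894, 0.707, a shrinkage of about 3, 11 and 29%.

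| d (SD) | Type I error, exercise test, set omitted | Power, 0.7 SD exercise effect: omitted / included | Power, 1.3 SD group-by-exercise: omitted / included |
|---|---|---|---|
| 0.25 | about 4% | 82% / 84% | 76% / 78% |
| 0.5 | about 3% | 77% / 84% | 70% / 78% |
| 1.0 | about 0.5% | 54% / 84% | 46% / 78% |

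**Step 2: pairing balanced 10/10 overall, without regard to group.** The number of users with a given pairing is hypergeometric.

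- Exact 5/5 split in each group: C(10,5)²/C(20,10) = 63,504/184,756 = 0.34.
- 7:3 against 3:7 or worse, either direction: 2 × (1 + 100 + 2,025 + 14,400)/184,756 = 33,052/184,756 = 0.18.

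At 7:3 against 3:7 the user mean moves by (0.7 − 0.3)d = 0.4d and the control mean by −0.4d, so the group-by-exercise estimate shifts by 0.8d. Simulated type I error, conditional on that split and with set omitted, is 6.5, 9.2 and 15.4%. Averaged over all allocations the shift is zero and type I error is 5%.

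**Step 3: set included.** The shift is zero and type I error is 5% at every split tested, given the same d in both groups.

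**The case against.** Several counter-arguments have force.

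- A reader might infer that the pairing is balanced only overall, or is unbalanced between groups. The protocol does not say so. Balance within group is unstated, not denied.
- A reader might also infer that the group-by-exercise estimate is biased. Under random pairing it is not. The shift is a chance imbalance in one realised sample, zero on average, with 5% type I error over allocations.
- With balanced sets, the raw contrast has the same true sampling variability whether or not set is modelled. Only its estimated SE is inflated, so the loss lies in the test and in standardised effects.
- The methods paragraph explains the choice of GEE and is not a closed list of terms. A SAP that is not shown may add more. That is fair for the model term, but a SAP cannot repair the pairing once scans are done.
- Crediting the balancing with removing order effects might be called plainly wrong. It is better called loose, since fresh pictures at the second scan do limit repeat exposure.
- Everything scales with d, which is unknown. At 0.25 SD the cost is about two points of power, and this is a pilot without a power target.
- The calculation needs one scan after each exercise condition. The footnotes to Table 1 also allow scans at Visits 1 and 3, and the table marks no exercise at Visit 1. The figures do not apply to anyone scanned that way.

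The wording also admits a harsher reading: one fixed set per condition, with only order balanced. Set would then be fully confounded with exercise, and no model term would help. The text does not establish this reading, but it should be worded so as to exclude it.

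**Conclusion.** The point holds as an improvement to the stated design and model, not as a demonstrated bias. The documents establish that set and exercise condition vary together within each person, that balance within each group is left open, and that the named model terms omit set.

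If the sets differ by 0.25 to 1.0 SD, omission costs between little and a great deal: 3 to 46% on the estimated SE, and 3 to 29% off standardised effects. The pooled raw exercise mean is safe under balanced pairing. The group-by-exercise comparison is exposed only to chance imbalance, and only if pairing is not balanced by group. In that case roughly one allocation in six is as uneven as 7:3 against 3:7 or worse.

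These sizes rest on the assumed d, on 10 analysed per group and on one scan per condition.

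**What to change.** **Stimuli section.** State that each image set is paired with each exercise condition in equal numbers within users and within controls, and that this removes set differences. That wording rules out one fixed set per condition.

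**General statistical methods, Aim 2.** Add the image set shown at each scan as a fixed factor in the exercise model. A common set term assumes a similar A-minus-B difference in users and controls. Within-group balance protects the group-by-exercise contrast if that assumption fails. The model term in turn helps if runs lost to motion or withdrawals disturb the planned balance.

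**Labels.** The Stimuli section calls one of the two conditions moderate, while the Exercise section describes light exercise. The two passages must be reconciled.

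**Cost.** One model degree of freedom and one allocation list per group, with no added participants or procedures.

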**Image Acquisition**

Collected images will include structural images for functional data overlay, diffusion tensor images for correlating fiber tract integrity with craving scores, resting functional images for baseline connectivity effects, and task-evoked functional images for examining image-induced regional brain activation. All images acquisitions do not involve contrast and are minimal risk. 128 T1 volumetric 3-D SPGR whole-brain sagittal images will be acquired from all study participants at 3 T with a SENSE head coil. Parameters: Flip = 20 degrees, TE = 4.2 ms, slice thickness = 1.2 mm, no skip, field of view (FOV) = 24x 24 cm, matrix size 256 x 256 pixels for an in-plane resolution = 0.88 mm. Whole brain 3-D images will be used for overlay of functional data in 3-D space. We will acquire whole-brain functional oblique slices of 4.5 mm thick covering the regions of interest (TE=35 ms, TR=2 s, Flip=790, matrix 64 x64. Images will be collected on the 3.0 T Philips scanner using a quadrature head coil. We will collect whole-brain axial slices of 4.5 mm thick with 0.5 mm skip. We will analyze fMRI data using the Brain Voyager QX software (Brain Innovation, Maastricht, The Netherlands) or other analysis package employing the general linear model (GLM) to construct statistical parametric maps SPMs to examine regional brain activation in response to photic stimulation and the semantic task. Preprocessing: 3-D motion correction (runs having over 2 mm translational motion or more than 1 degree rotational motion will be excluded), spatial smoothing (4 mm FWHM Gaussian kernel), temporal smoothing (linear trend removal and 3-Hz high pass filtering) (Skudlarski et al., 1999). Statistical threshold for activation will be a false discovery rate of 0.05, corrected for the number of multiple independent whole-brain comparisons. The stimulus paradigm time courses will be convolved with a hemodynamic response gamma function (Boynton et al., 1996). Following SPM construction, activation within a desired region of interest will be determined as the number of pixels reaching statistical threshold and the percent BOLD signal change within the activated pixel region. The method for choosing ROI's is defined below.

1. **Risks**

This study will include adults (18-35 years old).

Potential Risks of fMRI Imaging:

*Physical: -* Magnetic resonance procedures themselves do not utilize ionizing radiation, and there are no common physical risks to MRI procedures. Minor physical discomfort may occur while lying in the scanner.

*Psychological:* – Potential psychological risks include anxiety during various procedures. Some individuals (5-10%) become claustrophobic in the MR scanner, leading to premature termination of the study. Proposed measures to minimize imaging risks -- The Imaging Institute, including [name] group, has extensive experience in MRI research studies with adults. Our staff and imaging center personnel are very experienced in keeping participants comfortable during scanning procedures. Participants are carefully screened for indwelling metal or medical devices that might pose a danger in the scanner. We follow a complete and in-depth screening procedure designed to identify any participant with a mental health disorder that might make him/her particularly vulnerable to these procedures.

Potential Risk of Exercise Testing (VO2max)

To assess physical capability to perform exercise (walking and running), participant will be given a graded-treadmill test using age appropriate protocol. During the test, participant will be closely monitored and will be instructed to stop the test when they choose. The test will be stopped by the research team if their heart rate exceeds their maximum heart rate (220 – age). The test will be preceded with assessment performed by a physician or designated nurse and would include EKG to screen out participants with abnormal EKG response from the treadmill test.

The criteria include:

- ST-segment depression (defined as ≥1.0 mm of horizontal or down-sloping ST at 80 msec beyond the J point, suggesting myocardial ischemia)
- Ventricular arrhythmias, presenting as frequent multiform PVC, and especially in combination with ST depressions
- Heart rate response that >2 standard deviations (>20 beats/min) below the age-predicted maximal HR who are limited by volitional fatigue
- A change in Diastolic blood pressure >15 mmHg
- Anginal symptoms > 2 (out of 1-4 scale, corresponding to chest pains of perceptible but mild, moderate, moderately severe, and severe intensities, respectively).

Potential Risk of Exercise.

There is potential risk of injury caused by walking or jogging on the treadmill. The common symptoms include shortness of breath, or more severe, such as falling down. Also, there may be the rare instance of heart problems, such as a heart attack, that could be life threatening. We will do a fitness test to screen if each participant is capable to walk or run for 20 to 30 minutes.

Potential Risks of Genotyping.

There is a very low risk that genotyping information may be disclosed and participant could suffer potential embarrassment or economic harm.

Potential Social/Legal Risks.

There are potential social risks to participants if the confidentiality of the information they provide us is disclosed. For this reason, we follow strict confidentiality procedures.

1. **Reporting of Adverse Events or Unanticipated Problems involving Risk to Participants or Others**

An adverse event (AE) is any untoward medical occurrence in a participant, not necessarily having a causal relationship with the study. A serious adverse event (SAE) is any untoward medical occurrence that a) results in death, b) is life-threatening, c) requires inpatient hospitalization or prolongation of existing hospitalization, d) results in persistent or significant disability/incapacity, or e) is a congenital anomaly/birth defect.

AE’s are graded as:

- Mild (no limitation of usual activities)
- Moderate (some limitation)
- Severe (inability to carry out usual activities)

AE’s are attributed according to the relationship to the study procedures as:

- Not related
- Unlikely
- Possible
- Probable
- Definite

SAE’s are reported immediately by telephone to the VU IRB. Adverse events will be detected by clinical examinations by the studies clinical investigator. An Adverse Event Report form will be completed and returned to the VU IRB within 5 working days. Summary Reports are submitted to the VU IRB and will contain a) The number of adverse events and an explanation of how each event was handled, b) The number of complaints and how each complaint was handled, c) The number of participant withdrawals and an explanation of why the participant withdrew or was withdrawn, and d) The number of protocol violations and how each was handled.

1. **Study Withdrawal/Discontinuation**

Participants will be withdrawn from the study for safety considerations, non-compliance with study procedures, difficulties with scheduling or participation, excess movement or anxiety during scanning, or other reasons that the PI or co-investigators conclude will impair the scientific utility of the study. Participants will be provided an explanation if they are withdrawn from the study by the investigators.

1. **Statistical Considerations**

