**General statistical methods**

Percent BOLD signal change in the targeted ROIs, as well as demographic characteristics of the experimental and control group will be summarized using descriptive statistics. Given proposed group sizes of 10 participants (with no missing data), we expect to use parametric statistical analysis procedures. However, samples of this size are highly sensitive to outlier values, thus visualization and statistical investigations of parametric assumptions will be conducted. Because relative (greater or lesser) differences in activation rather than absolute values of those differences are of primary interest in this research, if distributions do not meet parametric assumptions, depending on the nature of the violations methods based on ranks will be used or outliers will be dealt with on a case-by-case basis.

Assuming multivariate normality and homogeneity assumptions are met, multivariate profile analysis (Tabachnick & Fidell, 2000) will be used to investigate differential patterns of ROI activation (profiles) between the two primary study groups of cannabis users and non-user controls (Primary Specific Aim 1). A statistically significant interaction effect of study group and ROI (e.g., insula, inferior frontal cortex, ventrolateral prefrontal cortex, parahippocampal gyrus, bilateral fusiform gyrus) will indicate statistically significant differences in activation (% BOLD signal change) profiles. Given a statistically significant interaction effect from an overall profile analysis, post-hoc tests controlling the experiment-wise Type I error rate will be used to determine precisely which component members of the profile (i.e., areas of activation or ROIs) are contributing to the overall profile difference, as well as the magnitude and direction of the specific component difference. These effect sizes will be used for statistical powering estimates in the planning of subsequent RO1 research.

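### The stated 3-Hz high-pass cut-off cannot be applied to functional images taken every 2 s with a 60-s task cycle, and the protocol does not say what value was meant

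*Protocol*

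**What the plan says.** The preprocessing list in the protocol, under Image Acquisition, names motion correction, spatial smoothing and "temporal smoothing (linear trend removal and 3-Hz high pass filtering". The same section gives the functional acquisition as "TE=35 ms, TR=2 s, Flip=790, matrix 64 x64". The task regressor is built from the block design: "The stimulus paradigm time courses will be convolved with a hemodynamic response gamma function".

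The design is set out under Stimuli. The protocol says "we will present images in 30-second blocks of 10 images each, displayed for 2500 milliseconds with a 500 millisecond interstimulus delay" and that it will "limit each scanner run to 3 minutes 30 seconds (i.e. 3 target stimulus 30 second blocks, 4 blurred Gaussian background blocks".

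Activation is then taken from the maps made after preprocessing. In a region of interest it is "determined as the number of pixels reaching statistical threshold and the percent BOLD signal change within the activated pixel region". Under General statistical methods, a significant interaction of group and region "will indicate statistically significant differences in activation (% BOLD signal change) profiles". The within-subject exercise analysis uses activation in the same way, and the resulting effect sizes are to be used to power the later grant application. No other cut-off, and no other unit for the filter, appears in the protocol.

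**The concern.** A high-pass filter is meant to remove slow drift and leave the task. It does so only if the cut-off lies below the task frequency, and it can be run only if the cut-off lies below half the sampling rate. The stated value fails both conditions by a wide margin. This is not detail left to an analysis plan: the protocol fixes a value, and the value is wrong.

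What is at stake is the BOLD side of the study: the count of activated pixels, the percent signal change, and the region-of-interest and whole-brain analyses. Whoever runs the analysis must replace the figure, and the protocol gives no basis for choosing the replacement. Some plausible replacements leave the task signal almost whole, and others remove about two thirds of it. If the choice is made after the data have been seen, it becomes an undeclared analysis decision. With about 10 participants per group and effect sizes as a key product, there is little precision to spare.

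**Working it through.** **Inputs from the protocol**

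- Sampling interval: 2 s (Image Acquisition).
- High-pass cut-off: 3 Hz (Image Acquisition).
- Target blocks: 3 per run, each 10 × (2.5 s + 0.5 s) = 30 s (Stimuli).
- Run length: 3 min 30 s = 210 s, with 4 background blocks (Stimuli).

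**Step 1: what the data can hold.** The sampling rate is 1/2 s = 0.5 Hz, so the Nyquist limit is 0.5/2 = 0.25 Hz. A run has 210/2 = 105 volumes, and its highest Fourier frequency is 52/210 = 0.248 Hz.

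**Step 2: where the task lies.** Each background block lasts (210 − 3 × 30)/4 = 30 s. One cycle is 30 + 30 = 60 s, so the task frequency is 1/60 = 0.0167 Hz, or 210/60 = 3.5 cycles per run.

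**Step 3: the stated cut-off against both.** 3/0.25 = 12 times Nyquist, and 3/0.0167 = 180 times the task frequency. No Fourier component of a 105-volume run lies at or above 3 Hz, so an ideal filter leaves nothing. A standard digital filter routine rejects the setting because the cut-off must be below 0.25 Hz. The stated figure therefore cannot be reproduced as a working filter.

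**Step 4: what other readings would do.** The protocol offers no alternative, so every reading here is an assumption. The block sequence (off, on, three times, then off) was convolved with a gamma response and sampled every 2 s. The protocol gives no gamma parameters, so three shapes were tried. The table shows the share of task-regressor variance left, relative to removal of the linear trend alone.

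| Assumed reading | Cut-off (Hz) | Variance kept |
|---|---|---|
| 0.003 Hz (cosine set) | 0.003 | about 99% |
| 128-s period (cosine set) | 0.0078 | about 93% |
| 1 cycle per run (Fourier pairs) | 1/210 = 0.0048 | about 94% |
| 2 cycles per run | 2/210 = 0.0095 | about 86% |
| 3 cycles per run | 3/210 = 0.0143 | about 31–35% |

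The last row is poor because 3 cycles per run sits next to the task's 3.5. Even there the result depends on the handling of the third cycle: if it is passed rather than removed, about 85% is kept.

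**Step 5: effect on precision.** Under white noise, the standard error of the task coefficient scales as 1/√(share kept). For 3 cycles per run this is 1/√0.35 = 1.69 to 1/√0.31 = 1.80, so about 1.7–1.8 times. With first-order autocorrelated noise and a least-squares fit, the ratio falls to about 1.58–1.68 at a correlation of 0.5 and 1.37–1.45 at 0.8. Both correlations are assumed values. For the 128-s cut-off under white noise it is 1/√0.93 = 1.04.

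**The case against.** The strongest reply is that this is an obvious slip with no practical effect. Software would refuse the value as soon as it was entered, before any result existed. The design is described as provisional, the choice of software is left open, and the raw images are not altered by a preprocessing constant. Much of this stands. A reader might infer from the text that the study would lose its whole task signal and have no outcome. The documents do not support that: the setting cannot be run, so it would be changed, and the data can be refiltered. Nor would every outcome be touched, since craving scores, demographic summaries and diffusion images do not pass through this filter.

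A reader might also infer that 3 cycles per run was intended, so that most of the task variance would be lost. The protocol does not mention cycles per run. It attaches a literature citation to the preprocessing, but that source is not at hand. The harmless reading of 0.003 Hz is equally open, so the damaging figures are one end of a range and not an expected result. The white-noise ratio is likewise an upper figure, because it shrinks when noise is positively autocorrelated.

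The reply does not make the text right. That the figure must be replaced is certain, and the protocol does not say by what.

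**Conclusion.** The cut-off is wrong as written. It is 12 times the Nyquist limit and 180 times the task frequency, and this follows from the protocol's own figures without any assumption. In practice the filter is unspecified, and it affects the BOLD outcomes only. How much the choice matters does rest on assumptions about the intended unit, the gamma response, the type of filter and the noise. Across the readings tried, the share of task variance kept runs from about 99% down to about 31%, and at the lower end the standard error is up to about 1.8 times as large under white noise. This is a correctable error in an analysis setting, most likely of unit or transcription. It should be put right before analysis, but it does not threaten the data collected.

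**What to change.** In the preprocessing text under Image Acquisition, replace the 3-Hz figure by a cut-off stated with its unit and set clearly below 0.0167 Hz. One example is 0.0078 Hz (a 128-s period), which keeps about 93% of the task variance; this value is a suggestion and does not come from the protocol. State also that the same filter is applied to the design matrix, so that data and regressor match. Make the change before the functional data are analysed.

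The cost is one figure and one sentence. No new data or participants are needed. The only downside is slightly more residual slow drift than a tighter filter would leave.
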